## Abstract

**Background:**

Physical inactivity is a main cause of childhood obesity which tracks into adulthood obesity, making it important to address early in life. Physical activity on prescription (PAP) is an evidence-based intervention that has shown good effect on physical activity levels in adults, but has not been evaluated in children with obesity. This project aims to evaluate the prerequisites, determinants, and feasibility of implementing PAP adapted to children with obesity and to explore children’s, parents’, and healthcare providers’ experiences of PAP.

**Methods:**

In the first phase of the project, healthcare providers and managers from 26 paediatric clinics in Region Västra Götaland, Sweden, will be invited to participate in a web-based survey and a subset of this sample for a focus group study. Findings from these two data collections will form the basis for adaptation of PAP to the target group and context. In a second phase, this adapted PAP intervention will be evaluated in a clinical study in a sample of approximately 60 children with obesity (ISO-BMI > 30) between 6 and 12 years of age and one of their parents/legal guardians. Implementation process and clinical outcomes will be assessed pre- and post-intervention and at 8 and 12 months’ follow-up. Implementation outcomes are the four core constructs of the Normalization Process Theory; coherence, cognitive participation, collective action, and reflexive monitoring; and appropriateness, acceptability, and feasibility of the PAP intervention. Additional implementation process outcomes are recruitment and attrition rates, intervention fidelity, dose, and adherence. Clinical outcomes are physical activity pattern, BMI, metabolic risk factors, health-related quality of life, sleep, and self-efficacy and motivation for physical activity. Lastly, we will explore the perspectives of children and parents in semi-structured interviews. Design and analysis of the included studies are guided by the Normalization Process Theory.

**Discussion:**

This project will provide new knowledge regarding the feasibility of PAP for children with obesity and about whether and how an evidence-based intervention can be fitted and adapted to new contexts and populations. The results may inform a larger scale trial and future implementation and may enhance the role of PAP in the management of obesity in paediatric health care in Sweden.

**Trial registration:**

ClinicalTrials.gov Identifier: NCT04847271, registered 14 April 2021.

**Supplementary Information:**

The online version contains supplementary material available at 10.1186/s40814-022-01075-3.

## Contributions to the literature

“Physical activity on prescription” is an evidence-based, complex intervention that is proven effective on adults, but neither implementation outcomes nor process has been evaluated in the context of paediatric health care.The hybrid-designed feasibility project combines process and outcome evaluations and uses both quantitative and qualitative methods.The use of Normalization Process Theory as a framework for the whole project will contribute to the literature on its application in various contexts.The project will contribute knowledge on the feasibility of whether and how an evidence-based intervention can be adapted and fitted to another population and context.

## Background

Childhood overweight and obesity is one of the most important global public health concerns in the twenty-first century. Prevalence has increased dramatically over the last four decades and remains high in many countries [1, 2]. The prevalence of overweight in European children aged 5–9 years was 28.9% in 2016, and the prevalence of obesity was 11.4% [3]. In Sweden, 21% of children aged 6–9 were overweight or obese in 2019, an increase by 14% since 2016 [4]. Of those 21%, 6% had obesity, up from 4% in 2016. Within this age group, the prevalence was twice as high in 9-year olds than in 6-year olds. There is also a gender difference, with an 11% obesity prevalence in boys versus 9% in girls [4]. Parent’s income level, education level, and country of birth are key predictors of lifestyle habits and obesity in children [5].

Physical inactivity is, alongside a poor diet, the main driver of childhood obesity [6]. As obesity in childhood tracks into adulthood [7, 8], addressing physical inactivity in early life is crucial. Particularly in middle childhood, social factors and physical inactivity are important risk factors for obesity [9]. Physical activity (i.e. any bodily movement that increases energy expenditure above a basal level [10]) has well-documented positive effects on physical and mental functions in children and is also important in relation to risk factors for lifestyle-related diseases, such as overweight/obesity, diabetes type 2, and to cardiovascular and metabolic risk factors [11, 12]. For children who are overweight or obese, physical activity has been shown to yield positive effects on weigh-related outcomes, especially when combined with dietary advice [13]. A recent systematic review of physical activity interventions in children with obesity showed effects on both body mass index (BMI) and physical activity [14]. Other reviews, however, are inconsistent, showing little to no effects on physical activity [15, 16].

In Sweden, national recommendations are that all children between 6 and 17 years should be physically active at least 60 min per day at a moderate-to-vigorous level [12], and that children who are insufficiently physically active should be offered physical activity counselling in health care [17]. The WHO also recommends limiting sedentary time and recreational screen time, which have shown detrimental effects on, e.g. physical fitness, metabolic health and school performance [18]. For children with obesity, physical activity at least 3 times/week at 75% of maximal heart frequency is recommended, for effects on lipids and insulin sensitivity [12]. Studies show that parents’ physical activity levels generally are linked to child physical activity levels, and parental support is perceived as crucial, indicating the benefit of involving parents in research on children [19–21].

Obesity is considered a complex multifactorial condition [22], and behaviour change interventions aiming to improve dietary intake, increase physical activity, and reduce sedentary behaviour are often prescribed and recommended [23]. One such intervention that aims to change physical activity behaviour is “physical activity on prescription” (PAP). This is an intervention developed in Sweden to promote physical activity and motivate the patient to increase their physical activity level [24]. Several studies have shown effectiveness of Swedish PAP in adult populations, including patients with overweight or obesity, measured as increased physical activity levels [25]. There is, however, a paucity of studies of PAP for children and adolescents. One small study investigated PAP in children with cerebral palsy and found PAP to be both feasible and leading to increased physical activity levels [25]. For children with obesity, no study has been identified that evaluates the implementation or effect of PAP. Before conducting a definite effectiveness trial, it is important to evaluate the feasibility and prerequisites for implementing this potentially behaviour-changing intervention in paediatric health care. The vulnerability of the patient group, the parental involvement, and the complexity of the intervention make it particularly important to investigate areas of uncertainty in a future effectiveness trial so that, e.g. recruitment, attrition, intervention fidelity, and other feasibility measures can be assessed and may be tweaked prior to a main trial.

When studying and implementing new interventions in a complex context such as health care, it is important to examine implementation determinants that can be used to develop an effective implementation strategy. Implementation determinants are factors that might prevent or enable improvements in professional practice [26] and are commonly used as an umbrella term for factors that hinder (barriers) and facilitate or enable (facilitators) implementation. They exist at several levels, including patient level, organisational level, and the wider environment/society [27]. Barriers for implementing PAP for adults that have been identified among Swedish primary healthcare providers include lack of knowledge about the intervention and lack of organisational support [28–30]. Facilitators include affirmative attitudes among colleagues and central and local supporting structures. For children, family support and parental role models are crucial when implementing physical activity, underscoring the need to involve parents in any efforts to promote physical activity [19, 31]. However, no study has investigated determinants for implementation of PAP for children with obesity.

This project addresses the above knowledge gaps. Increased knowledge and understanding of these factors are essential for successful implementation of PAP as an intervention for treatment of obesity in paediatric health care. The project will contribute important findings that can form the basis for implementation efforts in Region Västra Götaland, Sweden, and beyond. It will also provide knowledge about the feasibility of PAP for children with obesity, as well as about how an evidence-based intervention can be adapted to a new context and population and how implementation can be facilitated.

### Aims

The overarching aim of this project is to evaluate the prerequisites, determinants, and feasibility of implementing PAP for children with obesity in paediatric health care. Quantitative studies will investigate implementation and clinical outcomes, while qualitative studies will explore implementation determinants among different stakeholders.

Specific study objectives are as follows:Study 1: To examine how healthcare professionals and managers perceive working with PAP for children with obesity in terms of coherence, cognitive participation, collective action, and reflexive monitoring and how they perceive acceptability, appropriateness, and feasibility of a PAP intervention and, furthermore, to explore barriers and facilitators for working with PAP for children with obesity.Study 2: To explore experiences, barriers, and facilitators for using PAP for children with obesity among healthcare professionals and managers.Study 3: To evaluate the feasibility and acceptability of a PAP intervention for children with obesity on implementation outcomes and clinical outcomes, with physical activity pattern being the primary clinical outcome variable.Study 4: To explore children’s and parents’ experiences of participating in a PAP intervention, with a focus on perceived barriers and facilitators for implementing PAP.

Specific research questions are presented in Table 1.

**Table 1 Tab1:** Research questions

*Study*	*Preliminary title*	*Research questions*
1	Working with PAP for children with obesity in paediatric health care — a cross-sectional survey	How do healthcare professionals and managers perceive working with PAP for children with obesity in terms of coherence, cognitive participation, collective action, and reflexive monitoring?
		How do healthcare professionals and managers perceive PAP for children with obesity in terms of acceptability, appropriateness, and feasibility of the intervention?
		Is there a difference in the above variables between healthcare units, age groups, or professions?
		What are the perceived barriers and facilitators for working with PAP for children with obesity?
2	Experiences among healthcare professionals and managers of using PAP for children with obesity — a focus group study	What are the experiences of healthcare professionals and managers in paediatric clinics of working with PAP for children with obesity?
		What barriers and facilitators do they perceive related to implementing PAP for children with obesity?
		Which contextual factors do they consider important when working with PAP?
3	Evaluation of PAP for children with obesity on implementation and clinical outcomes — a single-arm intervention study	Do healthcare professionals’ and managers’ perceptions of PAP and working with PAP for children with obesity change after a PAP intervention?
		Do physical activity patterns of children with obesity and one of their parents change after participation in a PAP intervention?
		Is there a correlation between the child’s and their parent’s physical activity pattern?
		Is there a change in BMI, metabolic risk markers, health-related quality of life, sleep, or self-efficacy or motivation for physical activity after participation in a PAP intervention?
		What is the acceptability and feasibility of the intervention among children and parents?
4	Children’s and parents’ experiences of participating in a PAP intervention — an interview study	What are the experiences of children with obesity and their parents of participating in a PAP intervention?
		Which barriers and facilitators of implementing PAP do children and their parents perceive?
		How do children and parents perceive their (their child’s) behaviour change, if any, with particular emphasis on physical activity behaviour?

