#### Clinical outcomes

All clinical outcomes will be measured pre- and post-intervention and at 8 and 12 months’ after baseline. The primary clinical outcome will be physical activity level, measured as minutes per day spent in moderate to vigorous physical activity (MVPA) and assessed using the Axivity accelerometer (Axivity AX3, Axivity Ltd., UK). Accelometry is the most commonly used method in clinical and epidemiological research for objective measurement of physical activity, is easy to use for the study participant and the researcher, and has a high sensitivity for detecting changes in physical activity (30). The accelerometer will be placed above the child’s and parent’s hip in an elastic belt and worn 24 h per day for seven consecutive days. In this position, the accelerometer can be used to assess physical activity at different intensities. The accelerometer recording is accompanied by an activity diary to determine bedtime, non-wear time, and sport activities. A strict protocol for data quality assurance (malfunction, spurious data, wear time, valid days) will be used. A project coordinator will provide the accelerometer to the participants together with oral and written instructions, support the participants if necessary, and collect the accelerometer after use. Measurement procedure, quality assurance, data processing, and analysis will be supported by an experienced team at the Center for Health and Performance [58].

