Secondary clinical outcomes will be physical activity patterns (time spent in different types of activities and at different intensity levels, including sedentary time) measured with accelerometry; anthropometric measures, i.e. BMI; and waist circumference, collected from medical charts. Metabolic risk markers will be assessed via blood pressure measures and blood samples, including fasting plasma glucose, high- and low-density lipoprotein cholesterol, insulin resistance, and triglycerides. In addition, patient-reported health-related quality of life will be measured using KIDSCREEN-10 [59], and the child’s sleep will be measured using the Insomnia Severity Index (ISI) [60, 61]. Parents’ perception about their child’s sleep will be measured using the Pediatric Insomnia Severity Index (PISI) [62, 63]. The child’s self-efficacy for physical activity, and motivation for physical activity, will be measured with validated instruments adapted to children with obesity and parents and appropriately translated to Swedish [64–67]. Adverse events will be monitored and documented.

Demographic data on children will be collected at baseline, including age, gender, comorbidities, and country of birth. Data on participating parents/guardians include age, gender, BMI, comorbidities, country of birth, and education level.

To enable missing data analysis, demographic data will also be collected for those who decline participation, when possible.

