#### Clinical outcomes

Descriptive statistics will be used to summarise characteristics of the participants and will be presented as means with standard deviations or frequencies and percentages. For physical activity outcomes, raw accelerometer data will be processed and filtered in several steps to a measure of activity intensity (mg) [58]. Previously developed and tested calibration equations for body positions, activity type, and for activity intensities will be applied [70, 71]. Accelerometer data will be analysed in 3-s epochs in order to accurately detect normal variation in physical activity [58]. Continuous data on physical activity patterns at baseline, 4, 8, and 12 months, will be analysed using multivariate regression analysis for repeated measures, controlled for multicollinearity between intensity levels. To examine potential influences of demographic and parental factors (gender, age, education level, country of birth) on physical activity patterns, the models will be adjusted for these variables. Change in absolute BMI in kg/m^2^ and in metabolic risk markers in mmol/L will be calculated and analysed using mixed linear modelling. Standardised measures for the separate risk factors waist circumference, insulin resistance, systolic and diastolic blood pressure, high-density lipoprotein, and triglycerides will also be combined in a so-called MetS score and analysed using mixed linear modelling. Patient-reported outcomes will also be analysed using mixed linear modelling and adjusted for the same demographic and parental factors. Changes over time will be presented with 95% confidence intervals. The self-efficacy and motivation variables’ potential mediating role for physical activity will also be explored by including these parameters into the models as covariates. Statistical significance will be set at *p* < 0.05.

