A challenge when adapting a clinical intervention such as PAP that has been evaluated and found effective in another context is that adaptation by default means that intervention fidelity is not maintained [49]. Fidelity is considered important for implementation success [75] and an important part of a process evaluation [76]. However, a high degree of intervention fidelity requires strict adherence to a protocol and implies a top-down approach to implementation, whereas adaptation that involves engaging users and other stakeholders reflects a bottom-up approach [77]. This approach is not only more politically appealing from a social development perspective but is also likely to improve acceptability and feasibility of the intervention in the new context.

We chose physical activity level as primary clinical outcome because increasing physical activity is the main goal of the PAP intervention and because the effect of PAP on activity level has been established in adults [78]. We will assess physical activity objectively using accelerometers in this project as it reduces measurement errors associated with subjective methods, especially in children [58]. In addition, a robust measurement protocol will be applied to assure a high-quality standard, considering all steps from data collection to processing to achieve useful and reliable measures [58].

We will collect clinical outcome data immediately post-intervention and again at 8 and 12 months from baseline. It is well known that behaviour change takes time, and continued physical activity will be encouraged at the end of the intervention period. Conversely, it has also been shown that a positive change post-intervention, for example in BMI, may not be sustained in the long term [13].

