PAP has already been used at several paediatric healthcare units, to varied extents, both in Region Västra Götaland and elsewhere in Sweden. This, together with the fact that PAP is a well-established intervention for adults, constitutes a clinical advantage and should facilitate a wider implementation of the intervention, if found effective, throughout the region and, later, to other regions in Sweden and potentially elsewhere. This project is expected to generate new knowledge regarding the feasibility of adapting PAP to children, as well as about whether and how an evidence-based intervention can be fitted and adapted to new contexts and populations. The qualitative study findings will increase our understanding of implementation determinants, including contextual factors, and of childrens’ and parents’ experience of participating in a PAP intervention. The study results may form the basis for a larger scale clinical trial, may guide future implementation, and may potentially enhance the role of physical activity in the management of obesity in paediatric health care in Sweden. If the adapted PAP intervention shows positive results on physical activity levels and other outcomes for the children included in this study, the prospects are good for implementing the intervention in routine paediatric health care.

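### Study 3 states its primary clinical outcome inconsistently (activity pattern in the Aims, MVPA minutes per day in the Methods), and no stated analysis isolates MVPA

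*Protocol article*

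**What the plan says.** All references are to the protocol article.

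- **Aims, Study 3 objective:** the study is to be evaluated "with physical activity pattern being the primary clinical outcome variable".
- **Aims, Table 1, Study 3 research question:** "Do physical activity patterns of children with obesity and one of their parents change after participation in a PAP intervention". MVPA is not named, and child and parent appear together.
- **Data collection and outcomes, Clinical outcomes:** "The primary clinical outcome will be physical activity level, measured as minutes per day spent in moderate to vigorous physical activity (MVPA". Child and parent both wear the accelerometer.
- **Same section, next paragraph:** "Secondary clinical outcomes will be physical activity patterns (time spent in different types of activities and at different intensity levels, including sedentary time".
- **Same section, timing:** "All clinical outcomes will be measured pre- and post-intervention and at 8 and 12 months". No visit is ranked above another.
- **Data analysis, Clinical outcomes:** the data to be modelled are "Continuous data on physical activity patterns at baseline, 4, 8, and 12 months", in a multivariate repeated-measures regression that deals with collinearity among intensity levels. The section ends with a 0.05 significance threshold and also promises 95% confidence intervals for changes over time.
- **Discussion:** "We chose physical activity level as primary clinical outcome because increasing physical activity is the main goal of the PAP intervention".

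**The concern.** The same variable, activity pattern, is primary in the objective and secondary in the Methods. The two terms are not interchangeable. The Methods define level as one number (MVPA minutes per day) and pattern as a collection of quantities covering activity types, intensities and sedentary time.

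The inconsistency carries into the analysis. The Methods name MVPA as primary, but the analysis section describes a model for patterns across several intensity levels and four time points, without saying which coefficient or contrast answers the primary question. The person is also left open, because both child and parent are measured.

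An analyst could therefore report MVPA, sedentary time or another intensity class as the primary clinical result, in the child or the parent, and point to some part of the article in support. That choice should be closed before outcome data are seen. A later analysis plan cannot simply fill a gap here; it would have to overrule either the objective or the Methods.

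**Working it through.** **Step 1: set the statements side by side.**

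| Place | Term used | Status | Person |
|---|---|---|---|
| Aims, Study 3 objective | pattern | primary | not stated |
| Table 1, Study 3 | pattern | research question | child and one parent |
| Methods, outcomes | level (MVPA min/day) | primary | both measured |
| Methods, outcomes | pattern | secondary | not stated |
| Data analysis | pattern | only activity analysis given | not stated |
| Discussion | level | primary | not stated |

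The objective conflicts with the Methods and the Discussion. The research question and the analysis use the objective's term.

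**Step 2: is there a figure in the plan to reproduce?** No. The article gives no effect size, SD or power. The target of about 60 children is stated to rest on no formal calculation.

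**Step 3: illustrate what the open choice could cost.** Inputs from the article are a threshold of 0.05 and three follow-ups (4, 8 and 12 months). Assumptions are two-sided tests, no true change, four intensity classes for pattern, and a common correlation ρ between test statistics of 0, 0.5 or 0.8.

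For k independent tests, P(at least one p < 0.05) = 1 − 0.95^k:

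- k = 1: 0.050
- k = 3 (child MVPA, three follow-ups): 1 − 0.95^3 = 0.143
- k = 6 (child and parent MVPA, three follow-ups): 1 − 0.95^6 = 0.265
- k = 12 (four classes × three follow-ups): 1 − 0.95^12 = 0.460

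For correlated tests, z_j = √ρ·z_0 + √(1−ρ)·e_j with independent standard normal terms, counting draws in which any |z_j| exceeds 1.96 (200,000 draws):

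| k | ρ = 0 | ρ = 0.5 | ρ = 0.8 |
|---|---|---|---|
| 3 | 0.143 | 0.125 | 0.098 |
| 6 | 0.265 | 0.209 | 0.139 |
| 12 | 0.460 | 0.319 | 0.188 |

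Three changes from a shared baseline are correlated at 0.5 if all visits have equal variance and equal pairwise correlation, so the middle column is a reasonable centre for k = 3.

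**Step 4: direction.** Only favourable false positives would be presented as success, and these are roughly half of the total. For ρ = 0 they are 1 − 0.975^3 = 0.073 (k = 3) and 1 − 0.975^12 = 0.262 (k = 12). For ρ = 0.8 they are 0.049 and 0.094. One contrast gives 0.025.

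**The case against.** The strongest reply is that the intention can be recovered. Only the Methods give an operational definition, with a unit, a device and a wear period, and the Discussion agrees and gives a reason. The objective is one line without a metric. MVPA is presumably one of the intensity levels in the planned model, so it is not left without any analysis. This stands, and it lowers the severity. It does not remove the contradiction, because the research question and the analysis follow the objective's term.

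Four stronger readings are tempting, and the article does not support them.

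- A reader might infer that leaving the primary visit and multiplicity unstated is a defect in itself. A condensed article commonly leaves these to the full protocol or analysis plan, and a joint test of time in the repeated-measures model would not require choosing a visit. The silence matters here only because the primary variable is itself unsettled.
- A reader might infer that p < 0.05 governs every outcome in the project. The threshold stands only in the analysis section for clinical outcomes; the section for implementation outcomes states none.
- A reader might count some 17 secondary outcomes at three visits and quote 1 − 0.95^17 = 58% or 1 − 0.95^51 = 93%. Most of those outcomes (BMI, lipids, sleep, quality of life) are plainly labelled secondary and could not be mistaken for the primary one. Independence is also implausible.
- A reader might treat the Discussion's condition for routine implementation, that the intervention "shows positive results on physical activity levels and other outcomes for the children included in this study", as a decision rule. It is an optimistic remark. The recruitment section ties the decision on full-scale evaluation to feasibility uncertainties, and Strengths and limitations rules out effectiveness conclusions.

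**Conclusion.** The point holds as an internal contradiction about the primary clinical outcome of Study 3. It has two consequences: no stated analysis or contrast isolates MVPA, and the person whose activity is primary is not named.

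The possible cost is a false-positive chance of about 10–14% for child MVPA over three follow-ups, or about 19–46% if pattern means four intensity classes over three follow-ups, against 5% for one prespecified contrast. These ranges rest on the assumed correlations (0.8 to 0), two-sided tests and the assumed number of classes. They illustrate the room for choice and are not estimates for this study.

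Severity is moderate. This is a single-arm feasibility study with its own primary implementation outcomes, an acknowledged power limitation and no effectiveness claim.

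**What to change.** - **Aims, Study 3 objective:** replace the closing phrase with wording such as *the primary clinical outcome is the child's mean MVPA in minutes per day*.
- **Table 1, Study 3:** ask first whether the child's MVPA changes. Make activity patterns and the parent's activity separate, secondary questions.
- **Data analysis, Clinical outcomes:** state a repeated-measures model for child MVPA with one named primary contrast, for example baseline to 4 months, the end of the intervention. Another contrast would also serve if it is fixed before outcome data are seen. Keep the multivariate model for patterns, parent MVPA and the later visits as secondary, reported with the 95% confidence intervals already planned.
- **Registry:** check that the entry carries the same definition. The Methods already commit to amending it for important changes.
- **Minor wording note, Discussion:** soften the sentence on prospects for routine implementation so that it agrees with Strengths and limitations.

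The cost is wording only, with no extra data or participants. The downside is that fewer results can be headlined as primary.
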